#### Co-interventions

Additional wound debridement, cleansing or protection may be indicated during a dressing change and is allowed in all treatment arms, as this reflects real life. In case of an (impending) wound infection, the wound may be treated with iodine (Povidone- or Cadexomer iodine), to be applied beneath the allotted dressing material [19]. The type of iodine used will be recorded.

### Study outcomes

#### Primary endpoints

The primary endpoint with respect to the effectiveness of wound dressings in the treatment of DSWs is time to complete wound healing. We define wound healing as re-epithelialization of the total wound surface. We decided this is not the case until all crusts have come off. This endpoint is to be assessed by an independent investigator who is not aware of the treatment given. The second primary outcome is pain from the donor site area. It is documented by the patient on a Visual Analogue Scale (VAS), varying from 0 (no pain) to 10 (intolerable pain). This is scored daily for the first two weeks postoperatively and twice a week during the third and fourth week, in a patient-held diary. Both primary endpoints are meaningful and relevant to patients and were therefore used for the sample size calculation [20].

#### Secondary endpoints

As secondary endpoints we assess the occurrence of local complications, e.g. wound infections, based on clinical symptoms of infection, scarring at 12 weeks postoperatively (using Patient and Observer Scar Assessment Scale (POSAS) assessed by the patients themselves and researchers, treating physicians or specialized wound nurses) [21], patient satisfaction (varying from 1 (absolutely dissatisfied) to 10 (absolutely satisfied), and costs (material and nursing costs). Itching scores are also collected by using a VAS, ranging from 0 (no itching) to 10 (intolerable itching) and obtained through the patient-held diary.

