**Methods:**

A 14-center, six-armed randomized clinical trial is being carried out in the Netherlands. An a-priori power analysis and an anticipated dropout rate of 15% indicates that 50 patients per group are necessary, totaling 300 patients, to be able to detect a 25% quicker mean time to complete wound healing. Randomization has been computerized to ensure allocation concealment. Adult patients who need a split-skin grafting operation for any reason, leaving a donor site wound of at least 10 cm^2 ^are included and receive one of the following dressings: hydrocolloid, alginate, film, hydrofiber, silicone dressing, or paraffin gauze. No combinations of products from other intervention groups in this trial are allowed. Optimum application and changes of these dressings are pursued according to the protocol as supplied by the dressing manufacturers. Primary outcomes are days to complete wound healing and pain (using a Visual Analogue Scale). Secondary outcomes are adverse effects, scarring, patient satisfaction, and costs. Outcome assessors unaware of the treatment allocation will assess whether or not an outcome has occurred. Results will be analyzed according to the intention to treat principle. The first patient was randomized October 1, 2009.

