### Blinding

Blinding of patients and care-providers (e.g. doctors and nurses) is not possible because the treatment options cannot be masked. To overcome this possible source of performance bias, independent doctors and nurses of the outpatient clinic, who are unaware of the treatment allocation, will assess whether or not an endpoint has occurred [23].

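### The 12-week observer scar score may be given by treating physicians, whom the protocol says cannot be blinded, with no requirement that any observer be unaware of allocation

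*Protocol article*

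**What the plan says.** The Secondary endpoints section sets scarring at 12 weeks after surgery as a secondary endpoint, measured with the POSAS and "assessed by the patients themselves and researchers, treating physicians or specialized wound nurses". The scale thus has a patient part and an observer part. For the observer part, three kinds of rater are allowed, and none has to be independent or unaware of the dressing.

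The Blinding section begins: "Blinding of patients and care-providers (e.g. doctors and nurses) is not possible because the treatment options cannot be masked". Its remedy is that "independent doctors and nurses of the outpatient clinic, who are unaware of the treatment allocation, will assess whether or not an endpoint has occurred". The Methods part of the abstract makes a similar statement directly after listing the primary and secondary outcomes, scarring among them: "Outcome assessors unaware of the treatment allocation will assess whether or not an outcome has occurred". Neither statement names an exception.

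For the first primary endpoint, time to complete wound healing, the Primary endpoints section repeats the safeguard: "This endpoint is to be assessed by an independent investigator who is not aware of the treatment given". The scar endpoint has no such sentence.

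**The concern.** The protocol accepts that the people who treat the wound know the dressing, and it gives independent, unaware assessment as its protection. For the observer scar score it then admits one of the groups it has just called unblindable. A centre that follows the Secondary endpoints section to the letter may have the treating physician rate the scar, and it would comply with that section while departing from the safeguard in the Blinding section.

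The observer POSAS is a graded judgement. A rater who knows which dressing was used, and has a view of it, can shift the score in either direction without intending to. The protocol's Discussion itself names subjective outcome variables as a frequent difficulty in wound care research and says that the trial aims to measure its endpoints reliably and validly. Scarring is also part of the trial's stated question. A reader who meets the general blinding statement in the abstract may take the scar comparison to be assessor-blinded when, for some or many patients, it was not.

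**Working it through.** No figure in the plan bears on this point, so the check compares the protocol's statements outcome by outcome.

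1. **Who cannot be blinded.** Blinding section: patients and care-providers, with doctors and nurses given as examples of the latter.
2. **Who is the safeguard.** Blinding section: outpatient doctors and nurses who are independent and unaware of allocation. A doctor or nurse can therefore qualify. What separates the two groups is involvement in the patient's care and knowledge of the dressing, not job title.
3. **Who rates each outcome.**
   - Healing: an independent investigator unaware of treatment (Primary endpoints). Consistent with item 2.
   - Pain: the patient, in a diary (Primary endpoints). Unblinded by item 1.
   - Itching, satisfaction and the patient POSAS: patient ratings (Secondary endpoints; for satisfaction this follows from its nature). Unblinded by item 1.
   - Local complications: based on clinical symptoms; the assessor is not named.
   - Observer POSAS: a researcher, a treating physician or a specialized wound nurse, with no condition attached (Secondary endpoints).
4. **Each observer category against items 1 and 2.**
   - Treating physician: a care-provider by definition, so excluded by item 1 and unable to meet item 2. This is a direct conflict.
   - Researcher: status not stated. The Wound treatment and Data analysis sections say that crossovers are recorded and patients are returned to the allotted dressing, so at least some of the study team must know the allocation. That any particular scar rater knows it is an inference.
   - Specialized wound nurse: status not stated. The Discussion says that specialized nurses will predominantly assess healing, which is to be assessed unaware of treatment. This category can therefore be compatible with item 2, but nothing in the scar wording requires it.
5. **Could the score be given blind?** The Background expects these wounds to re-epithelialize in 7 to 21 days, and the Discussion urges centres to keep to the same dressing type until healing is complete. Twelve weeks is 12 × 7 = 84 days, which is 84 − 21 = 63 days after the upper end of that range. In most patients no dressing should still be in place to reveal the arm. An observer who did not treat the patient could then rate the scar without knowing the allocation.

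**The case against.** The strongest reply is that the general statements speak of whether an endpoint or outcome has occurred. That is the language of events. It suits complete healing and perhaps infection, but not a scar scale, and the Primary endpoints section attaches the unaware assessor to healing alone. On this reading the Blinding section never promised a blinded scar score, and there is no contradiction. The reading is fair, but it does not remove the point. Neither general statement is limited to healing, and the one in the abstract follows a list that includes scarring. If the narrow reading is what was meant, the observer POSAS has no blinding safeguard at all, and the same change is needed.

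A second reply is that wound nurses and researchers have not been shown to be unblinded. That stands. The conflict is established for treating physicians. For the other two categories the fault is only that no condition is set, and a researcher or nurse who did not treat the patient and does not know the dressing would be acceptable.

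A third reply is that nothing says the outpatient assessors see patients at 12 weeks, so the ease of a blinded score is partly assumed. That also stands, and it is why the fix carries a scheduling cost.

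A reader might go further and infer that pain, a primary outcome, is misrepresented as assessor-blinded. The documents do not support this. The protocol says "The second primary outcome is pain from the donor site area" and that "It is documented by the patient on a Visual Analogue Scale (VAS"), and the Blinding section says openly that patients are not blinded. Self-report is the natural way to measure pain, and describing it differently would change no result. A reader might also fault the Blinding section for naming performance bias where independent assessment addresses detection bias. That is a slip of terminology with no effect on conduct or analysis.

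**Conclusion.** The point holds for the observer part of the 12-week POSAS. As written, the Secondary endpoints section permits a rater whom the Blinding section says cannot be blinded, and it sets no condition of independence or unawareness for the other two. The result is an avoidable opening for detection bias in one component of one secondary endpoint. The healing endpoint is not affected, and the handling of pain is disclosed.

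No numerical size can be given. The documents do not say how often treating physicians would do the rating, whether raters would favour particular dressings, or whether any such preference would be shared across 14 centres and six arms. An inflated error rate could be calculated only from a bias chosen by the reviewer, and it would say nothing about this trial.

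The conclusion rests on two readings: that a treating physician is a care-provider in the sense of the Blinding section, and that the general blinding statements, which state no exception, were meant to reach the scar outcome. The first is plain. If the second is wrong, the contradiction becomes a missing safeguard, with the same remedy.

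**What to change.** In the Secondary endpoints section, require that the observer POSAS be scored by an independent assessor who is unaware of allocation, and remove treating physicians from the list of raters. The assessor may be one of the outpatient doctors or nurses described in the Blinding section, or a wound nurse or researcher who took no part in that patient's care and does not know the dressing. Researchers and wound nurses need not be removed as categories; it is enough to attach the condition to them.

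As a minor clarification, limit the blinding statements in the abstract and the Blinding section to wound healing and the observer scar score. Add one sentence saying that pain, itching, satisfaction and the patient POSAS are self-reports by patients who know their dressing.

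The cost is a few changes of wording and a small scheduling burden at 12 weeks, since each centre must have an unaware assessor available for that visit. Treatment, sample size and analysis are unchanged. If a centre cannot supply such an assessor, its observer scores should be declared unblinded.

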### Randomization

Patients are to be randomized in the operation theatre, just after the skin harvest and hemostasis, and before the DSW is to be dressed. In each contributing center an appointed officer performs the randomization using an online computer software program (ALEA NKI-AVL, Amsterdam, The Netherlands, Release: 2.2.) to ensure allocation concealment. The trial is stratified by center, with a balanced allocation ratio for each treatment arm using a biased coin [22]. The biased coin method preserves most of the unpredictability associated with simple randomization [22].

### Blinding

Blinding of patients and care-providers (e.g. doctors and nurses) is not possible because the treatment options cannot be masked. To overcome this possible source of performance bias, independent doctors and nurses of the outpatient clinic, who are unaware of the treatment allocation, will assess whether or not an endpoint has occurred [23].

### Sample size

The study size calculation (using nQuery Advisor version 7.0, Statistical Solutions Ltd, Cork, Ireland) was based on two primary outcomes using a one-way analysis of variance. To detect a 25% quicker mean wound healing, which is in agreement with the study of Wiechula [2], and with a 5% significance level, a power of 90%, and a standard deviation (SD) of 3 days, a sample size of 50 patients per group is necessary, given an anticipated dropout rate of 15%. This number also allows detection of a minimum difference in pain scores of 2.0 or greater (with a SD of 2) on the VAS and discernment of a cost difference of €2 per day. To recruit this number of patients an 18-month inclusion period is anticipated based on the performed number of SSGs as estimated by each of the 14 co-operating hospitals.

### Data collection

The coordination center designed a standardized case record form (CRF) and distributes this in a paper-based or electronic version. The latter one is made available through a secured website, http://www.rembrandt-trial.nl (using Joomla, an open-source website software package), which also facilitates remote patient randomization and data entry. We collect copies of all completed forms from the co-operating hospitals and maintain the database using SPSS software (PASW statistics version 18.0, IBM, Armonk, NY, USA). Data are collected on baseline demographic and clinical patient characteristics of each group, whether the patients receive the allotted treatment and complete the study protocol, and are analyzed for the primary outcomes. Patients whose treatment deviates from the initial allocation will be described together with the reasons for this. Data on all important adverse events or side effects in each intervention group are recorded as well. Data from the patient-held diaries will be returned to the coordinating center. Double data entry will be conducted by [name] and [name], and compared using the SPSS Data Entry Builder program (Release 4.0.2). We will resolve any discrepancies by discussion and by re-checking the data.

### Data monitoring

Data completeness is reviewed weekly, and reminders or queries are sent timely. [name] and [name] visit the cooperating hospitals on a regular basis to promote the trial and to be closely associated with the data collection. Thus, an accurate and complete data set is ensured. Because no (serious) adverse effects were expected from the commercially available dressings that would require interim analysis, we refrained from installing a data safety monitoring board.

### Data analysis

Data coding and analysis will be carried out using SPSS software (PASW statistics version 18.0, IBM, Armonk, NY, USA). Differences in outcome variables will be analyzed on an intention-to-treat basis. A general linear model will be used to analyze the differences between the treatment arms for the various endpoints measured repeatedly, as the data are likely to be unequally distributed. Differences in wound healing time between the dressing groups will be examined using the Kaplan-Meier method and the Mantel-Cox log-rank test. Data analysis will be conducted by the authors and replicated by the Clinical Research Unit of the coordinating hospital. We will record any crossovers and make sure the patient returns to the initially allotted dressing. Missing data are dealt with by using the Generalized Estimating Equations model in our statistical analysis.

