### Design and setting

We designed a national, 14-center RCT with six treatment groups in the Netherlands (Figure 1). The coordinating center (Academic Medical Center at the University of Amsterdam) invited hospitals (i.e. departments of surgery, plastic surgery and otorhinolaryngology) and burns centers to participate in the trial, resulting in 13 contributing hospitals (4 university hospitals, 5 teaching clinics and 4 general hospitals) and 1 burns center.

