## Discussion

In current clinical practice, a 'standard' wound such as a DSW does not appear to be associated with a uniform dressing choice [8]. Also the systematic reviews of available literature report a large clinical heterogeneity among the available trials [1,2,6,7]. To date, available evidence allows the tentative conclusion that dressings creating a moist environment seem to be preferable over gauze-based dressings in the management of DSWs. This recommendation is tentatively formulated because strong recommendations for clinical practice are hard to draw, mainly due to the poor quality and small sample sizes of the available trials. Therefore, most systematic reviews recommend new and large randomized clinical trials [2,6,7].

However, doing research in the realm of wound care involves much more than simply comparing wound care products in eligible patients. It poses many methodological and practical challenges in the design and execution of trials [24].

The first challenge is the design of our, intentionally pragmatic, RCT. To enhance the applicability and generalizability of the results of this trial, we chose a multicenter trial design and recruited patients from low- and high-volume centers like teaching hospitals and burns centers. We realize that for many surgical procedures, patients have better outcomes in high-volume centers [25-29]. However, split-skin grafting is a rather common procedure, also in smaller hospitals. Second, we are forbearing regarding local clinical care, for example by allowing several brands within each dressing group, different depths of skin grafting, and different methods of hemostasis. This helps mimicking 'real life', at the cost of losing some contrast between the six treatment arms.

Although we are liberal and pragmatic at some points, we feel we need to and can be strict in others. We urge the contributing centers to adhere to the same dressing type until complete wound healing is reached. This allows us to appreciate the true effects of each of the dressing types studied. Some argue this is not reflecting common practice [30], in which the dressing type is changed in response to any change in the clinical condition of the wound during the healing process. We do not think this will be a frequently occurring issue since these superficial DSWs usually have fairly short healing times. The protocol does allow for an antiseptic agent to be added in case of an (impending) wound infection.

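### Randomization is stratified by center, but the named healing test has no center strata: still valid, and less efficient than it could be if centers differ

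*Protocol article*

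**What the plan says.** **Design.** Design and setting: "We designed a national, 14-center RCT with six treatment groups in the Netherlands". The centers are 4 university, 5 teaching and 4 general hospitals and one burns center. Randomization: "The trial is stratified by center, with a balanced allocation ratio for each treatment arm using a biased coin". Center is the only stratification factor named.

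**Analysis.** Under Data analysis, the first primary endpoint is handled thus: "Differences in wound healing time between the dressing groups will be examined using the Kaplan-Meier method and the Mantel-Cox log-rank test". For pain and other repeated outcomes: "A general linear model will be used to analyze the differences between the treatment arms for the various endpoints measured repeatedly". On incomplete data: "Missing data are dealt with by using the Generalized Estimating Equations model in our statistical analysis". None of these sentences mentions center, strata or any covariate.

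**Sample size.** The calculation "was based on two primary outcomes using a one-way analysis of variance", which has no center factor either.

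**Sources of center variation.** Surgical procedure ties the harvesting instrument to local practice, states graft thickness as a preference, and leaves hemostasis to the surgeon. The Discussion accepts variation in brand, depth and hemostasis as the price of a pragmatic trial. No ICC or between-center variance is given.

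**The concern.** Stratified randomization makes the arms alike in their mix of centers. If center predicts healing time, the arm comparison is then more precise than a simple random split would give. A test that ignores center does not see this: it counts the center differences as noise when it computes its variance. The nominal 5% test then rejects a true null less often than 5%, and the arm comparison is less sharp than it could be.

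What is at stake is efficiency in a six-arm trial with about 42 evaluable patients per arm. The choice of strata, and any merging of small centers, is also best fixed before data are seen, because choosing among center groupings afterwards leaves room for selection.

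**Working it through.** **1. The plan's own figure.** With 15% dropout, 50 per group leaves 50 × 0.85 = 42.5 evaluable, or 255 in all. For a one-way ANOVA with six arms, α = 0.05 and SD 3 days, the noncentrality is λ = n·Σ(μᵢ − μ̄)²/σ², and 90% power on 5 and 249 degrees of freedom needs λ ≈ 16.84. The target is stated only as "To detect a 25% quicker mean wound healing", without a reference mean or a pattern for the six means, so the figure can be matched but not uniquely reproduced:

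| Pattern of means (range d) | Σ(μᵢ − μ̄)² | d at 90% power | Implied reference mean (d/0.25) |
|---|---|---|---|
| One arm differs | 5d²/6 | 2.07 days | 8.3 days |
| Evenly spaced | 0.7d² | 2.26 days | 9.0 days |
| Two extremes, rest in the middle | d²/2 | 2.67 days | 10.7 days |

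The first pattern with d = 2.07 is used below. Check: 42.5 × (5/6) × 2.069²/9 = 16.85.

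**2. Direction, by formula.** Let ρ be the share of total variance due to center. With perfect balance within centers, the between-arm mean square has null expectation σ²(1 − ρ), while the residual of an ANOVA without center stays near σ². The rejection rate is then about P(F₅,₂₄₉ > 2.25/(1 − ρ)): 5.0% at ρ = 0, 4.6% at 0.02, 4.0% at 0.05, 3.1% at 0.10 and 1.7% at 0.20. A biased coin balances less than perfectly, so the true reduction should be smaller.

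**3. Size, by simulation.** From the documents: 14 centers, 6 arms, 255 evaluable patients, SD 3 days. Assumed: center sizes of 5 to 40, a biased coin with probability 0.75 within center, normal healing times, no censoring, whole-day recording for the log-rank, total SD held at 3, and ICC from 0 to 0.20. There were 3,000 runs per cell; Monte Carlo error is about 0.4 points for type I error and 0.6 for power.

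| ICC | Type I, unstratified log-rank | Type I, stratified | Power, unstratified | Power, stratified | Gain from strata |
|---|---|---|---|---|---|
| 0 | 5.7% | 5.3% | 86.1% | 84.5% | −1.6 |
| 0.02 | 5.6% | 5.3% | 86.7% | 85.6% | −1.0 |
| 0.05 | 5.1% | 5.7% | 86.5% | 86.5% | 0.0 |
| 0.10 | 3.7% | 4.6% | 87.4% | 88.8% | +1.4 |
| 0.20 | 3.1% | 5.8% | 86.6% | 91.6% | +5.0 |

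(Gains are taken from unrounded rates.)

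ANOVA shows the same pattern. Power without and with center is 89.2% and 88.6% at ICC 0, 90.4% and 91.2% at 0.05, 90.4% and 92.0% at 0.10, and 90.2% and 95.2% at 0.20.

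**4. Sensitivity.** A separate simulation with equal centers (3 patients per arm per center, 252 evaluable, means spread over 2.69 days, 1,500 runs) gave unstratified type I error of 4.3% and 2.5% at ICC 0.10 and 0.20, with gains of 87.6 − 84.7 = 2.9 and 90.7 − 86.4 = 4.3 points. At ICC 0, stratifying cost 87.1 − 85.6 = 1.5 points. Direction and rough size agree. The gain shrinks when power is already high: with one arm faster by 2.5 days in the unequal-center setting (2,000 runs), it is 98.5 − 96.7 = 1.8 points at ICC 0.20.

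**5. Cell sizes.** 300/14 ≈ 21 randomized patients per center, and 255/(14 × 6) ≈ 3 evaluable per arm per center. Small centers will have empty cells.

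**The case against.** **Silence is not omission.** The article never calls its log-rank test unstratified. It is a summary, and strata and covariates are often left to a fuller document. For pain this stands: no covariates of any kind are listed, and either a general linear model or GEE can carry a center term. A reader might infer that the pain analysis ignores center, but the text does not establish it. For healing the objection is weaker, because a specific test is named for a primary endpoint and, as named, it leaves out the one factor used in randomization.

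**Center effects are not shown.** The Discussion remarks that "We realize that for many surgical procedures, patients have better outcomes in high-volume centers". A reader might take this as an admission that healing differs by center here. It concerns surgery in general, and the authors go on to say that skin grafting is also common in smaller hospitals. Hemostasis may vary by surgeon rather than by center, and the preferred graft thickness, the limited harvest sites and the staff instruction all narrow differences. Center effects are therefore plausible but unquantified.

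**No planned power is lost.** This also stands if the SD of 3 days already includes center variation: unstratified power stays between 86.1% and 87.4% over the whole ICC range. What is given up is a possible gain.

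**The remedy is not free.** Stratifying loses a little power when centers are alike, and thin cells call for a pooling rule.

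**Conclusion.** The point holds in conditional form. The design balances on center, and the named healing test does not use it. If centers differ, the test stays valid but is conservative: about 3.7% and 3.1% type I error, with about 1.4 and 5 power points forgone, at assumed ICCs of 0.10 and 0.20. At 0.05 the two tests break even, and below that the unstratified test is slightly ahead. These figures rest on the assumed center sizes, coin probability, normal healing times and absence of censoring, and above all on an ICC that the protocol does not give.

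Stronger readings are tempting but unsupported. It does not follow that the tests are conservative and underpowered whatever the centers look like, nor that the true type I error lies below 5% as a matter of fact. Nor are the intervals wrong: if centers differ, they are wider than necessary. For pain the gap calls for clarification. Power there is not at risk, since a difference of 2.0 with SD 2 needs 21 to 34 evaluable patients per group under the three patterns above, against 42.5 expected.

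This is a worthwhile improvement to a primary analysis, not a threat to its validity.

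**What to change.** Under Data analysis, make the primary healing test a log-rank test stratified by center, or a Cox model stratified by center. Name center as a factor (fixed or random) in the model for pain and in those for the other continuous outcomes. State, before data are examined, a rule for pooling very small centers, based on patient numbers and not on outcomes.

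The cost is a short change of wording plus the pooling rule. Center is known for every patient because randomization uses it. If centers turn out not to differ, the stratified test gives up about 1.5 points of power; if the ICC is near 0.20 it gains about 5.

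### The plan says GEE deals with missing pain diary entries, which unweighted GEE does not in general do, and it leaves unclear which of two models gives the primary pain result

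*Protocol article*

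**What the plan says.** The Primary endpoints section makes pain co-primary: "The second primary outcome is pain from the donor site area". On the schedule it says: "This is scored daily for the first two weeks postoperatively and twice a week during the third and fourth week, in a patient-held diary". That is about 18 ratings per patient.

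Three sentences in the Data analysis section then govern this outcome:

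- The model: "A general linear model will be used to analyze the differences between the treatment arms for the various endpoints measured repeatedly". The reason follows directly: "as the data are likely to be unequally distributed".
- Incomplete data: "Missing data are dealt with by using the Generalized Estimating Equations model in our statistical analysis".
- The analysis principle: "Differences in outcome variables will be analyzed on an intention-to-treat basis".

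Healing time is handled separately, by Kaplan-Meier and the log-rank test. The Sample size section expects 15% dropout, while the Data monitoring section describes weekly completeness checks and regards a complete data set as ensured. The Data analysis section does not link the general linear model to GEE.

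**The concern.** Three statements do not hold up.

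1. **GEE is presented as the remedy for missing data.** It is an estimating method for correlated outcomes. Without weighting or imputation it uses the ratings that exist and gives no general protection when absence is related to pain.
2. **The reason for the general linear model does not lead to it.** That model assumes normal errors with constant variance. If the phrase describes skewed or unequally variable scores, it argues against the model. If it means unbalanced or unequally spaced ratings, it still gives no ground for preferring this model.
3. **Two models are named for one primary outcome.** Nothing says which gives the reported pain comparison, and the choice could be made after the results are seen.

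Patients are not blinded and fill in the diary themselves. It is plausible, though not documented, that a diary stops because pain has gone or is bad, and that this differs between dressings. What is at stake is one of the two primary comparisons.

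**Working it through.** **Inputs from the protocol article.** Ratings per patient: 14 daily + 2 × 2 twice-weekly = 18 (Primary endpoints). Planned size: 50 per group with 15% dropout, so 50 × 0.85 = 42.5 evaluable; pain difference 2.0 with SD 2 (Sample size). The article gives no rate or mechanism for missing diary entries and no working correlation.

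**The plan's own pain figure.** In a six-group one-way ANOVA with 42 per group, two arms 2.0 apart and the other four midway, the noncentrality is 42 × (1² + 1²) / 2² = 21. Power is about 96%, so the Sample size statement on pain holds and this point does not touch it.

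**Why GEE does not deal with missing data.** Unweighted GEE solves Σ Dᵢ′ Vᵢ⁻¹ (yᵢ − μᵢ) = 0 over the observed ratings. For this to be centred on the true means in general, ratings that are observed must have the same mean, given the covariates, as those that are not. If a diary stops because of an earlier rating, later ratings come from a selected group. Under an independence working correlation each rating enters on its own, so the selection passes straight into the estimate. With a working correlation close to the true one, the patient's earlier ratings partly correct for it. For normal data with the correct V the equations match the likelihood score, which explains the small bias seen below.

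**Size under assumed mechanisms.** Simulation of two arms of 5,000 patients, 18 ratings, SD 2, true constant difference 1.0, one run per cell. The true within-patient correlation was either exchangeable (0.6) or autoregressive (0.85 to the power of the gap in days). Entries are the GEE estimate minus the full-data estimate.

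| Assumed missingness | Ratings missing | Exchangeable truth: GEE independence / exchangeable | Autoregressive truth: GEE independence / exchangeable |
|---|---|---|---|
| Completely at random | 20% | +0.007 / +0.004 | −0.001 / 0.000 |
| Completely at random within arm, rates differ by arm | 24–25% | +0.005 / −0.007 | +0.004 / −0.009 |
| Depends on previous rating, same in both arms | 38–39% | −0.155 / 0.000 | −0.077 / +0.013 |
| Depends on previous rating in one arm, constant in the other | 33% | −0.497 / +0.012 | −0.352 / +0.037 |
| Depends on the unseen current rating in one arm, constant in the other | 32–33% | −0.583 / −0.140 | −0.411 / −0.084 |

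**Smaller simulations.** These used 400 per arm, 25 runs, random-intercept and residual SD 1.4 each, and dropout driven by recorded ratings.

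- In one set the true differences were 0.83 and 0.87. GEE with independence gave 0.68 and 0.65; a mixed model gave 0.83 and 0.87.
- In another the true difference was 0.85. GEE with independence gave 0.78 (low pain stops the diary) and 0.68 (high pain stops it); GEE with exchangeable correlation gave 0.87 and 0.81.

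The random-intercept structure of these data suits a simple mixed model.

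**Caveat on size.** In the last three rows of the table only 39% to 48% of patients had complete diaries, so 52% to 61% stopped early. That is far more than the 15% dropout the plan expects. The rows show how the bias behaves; they do not forecast this trial.

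**The case against.** The strongest reply is that GEE may do well here. It was unbiased to within 0.01 when entries were missing completely at random, including when rates differed by arm. With an exchangeable working correlation it stayed within 0.04 in the table when missingness depended on earlier pain. This stands: a reader might infer that the pain comparison is biased whenever entries are missing, and the document does not support that. The larger figures need pain-related missingness together with an independence working correlation, or missingness that depends on unseen pain.

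The wording also allows a milder reading. The article never says the data are non-normal, and its phrase could mean unbalanced or unequally spaced, which the diary schedule is. GEE extends the generalized linear model, so the two sentences may loosely describe one GEE analysis, and GEE with robust standard errors tolerates non-normal scores. On that reading the second and third statements become a wording correction. The claim about missing data remains.

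Two further inferences are tempting and should be resisted:

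- **That a repeated-measures general linear model would drop every patient with a gap in the diary, against intention to treat.** The article does not state listwise deletion, and GEE uses all observed ratings.
- **That averaging 18 ratings would dilute an early effect and destroy power.** The article states neither an averaging rule nor an effect confined to the early ratings.

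Finally, working correlation, covariance structure and sensitivity analyses commonly sit in an analysis plan. Their absence from a condensed article is not the point. The point is what the article affirmatively states.

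**Conclusion.** The concern holds in a limited form. The GEE sentence claims a protection that unweighted GEE does not in general give, the reason offered for the general linear model does not support it, and the text does not say which model decides the pain outcome.

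The pain comparison may be biased if diary entries are missing in relation to pain. Per 1.0 point of true difference, and under the assumed mechanisms and loss in the table:

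- missingness driven by earlier ratings: 0.00 to 0.04 with exchangeable correlation; with independence, a shift of 0.08 to 0.16 towards zero if the mechanism is the same in both arms and 0.35 to 0.50 if it differs by arm;
- missingness driven by unseen ratings and differing by arm: 0.08 to 0.14 towards zero with exchangeable correlation and 0.41 to 0.58 with independence.

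Direction and size in this trial cannot be known from the document. Healing time, the sample size and data collection are unaffected.

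**What to change.** Replace the general linear model and GEE sentences with one primary analysis of pain:

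- a likelihood-based linear mixed model on all observed ratings, with arm, time, arm-by-time and center (the stratification factor), and a covariance structure fixed in advance. An unstructured matrix over 18 ratings has 18 × 19 / 2 = 171 parameters for 300 patients, so a fallback such as autoregressive should be named;
- the missingness assumption stated: valid when missingness depends on observed ratings, given a correct model;
- one named primary pain contrast, for example the model-estimated mean VAS over days 1–14, with weeks 3–4 secondary;
- a sensitivity analysis for entries missing not at random.

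If GEE is preferred, use weighted GEE or GEE after multiple imputation, and say so. Settle this before the pain data are analyzed.

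For the mixed model the cost is wording and slightly more analysis work, with the same data and the named software. The downside is reliance on the model's covariance and distributional assumptions, which a bounded 0–10 score may strain as pain subsides. Weighting or imputation instead relies on a correct dropout or imputation model.
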